## Abstract

**Background:**

Colorectal cancer is the third most common cause of cancer death in both males and females in England. A national bowel cancer screening programme was rolled out in England between 2006 and 2010. In the post-randomised controlled trials epoch, assessment of the impact of the programme using observational studies is needed.

This study protocol was set up at the request of the UK Policy Research Unit in Cancer Awareness, Screening and Early Diagnosis to evaluate the effect of the current bowel cancer screening programme on incidence of advanced primary colorectal cancer.

**Methods/Design:**

All incident cases of primary colorectal cancer in England will be included. Cases will be matched to controls with respect to sex, age, area of registration and year of first invitation to screening. Each evaluation round will cover a 2-year period, starting from January 2012, and ongoing thereafter. In the first instance, a pilot will be carried out in a single region. Variables related to colorectal tumour pathology will be obtained to enable selection and matching of cases and controls, and to allow analyses stratification by anatomical subsite within the bowel. Cases at Duke’s stage B or worse will be considered as "advanced stage". The influence of sex will also be investigated. The incidence ratio observed in randomised controlled trials between controls (not invited) and non-attender invitees will be used to correct for self-selection bias overall. Screening participation at other national screening programmes (cervical, breast) will also be collected to derive a more contemporaneous adjustment factor for self-selection bias and assess consistency in self-selection correction in female patients.

Full ethical approval was obtained from the Health Research Authority.

**Discussion:**

The case–control design is potentially prone to a number of biases. The size of the planned study, the design specifications and the development of analytical strategies to cope with bias should enable us to obtain accurate estimates of reduction in incidence of advanced stage disease. The results of analyses by sex and anatomical subsite may highlight the potential need for sex-specific recommendations in the programme.

## Background

In England, colorectal cancer (CRC) is the third most common cancer in men after prostate and lung cancer and in women, after breast and lung cancer [1].

Meta-analyses of the randomised controlled trials (RCTs) have demonstrated the efficacy of biennial screening with guaiac faecal occult blood test (gFOBt) for haemoglobin in reducing *mortality* from CRC (rate ratio = 0.88, 95% CI 0.83-0.94, reviewed in [2]), while generally no significant effect of screening on *incidence* was found after 14 to 20 years of follow-up. Only one trial, performed in the USA, demonstrated any significant reduction in CRC incidence, but the validity of this result may be limited due to the fact that an unusually large proportion of subjects in the intervention arm underwent colonoscopy [3]. However, in all the trials, the reduction in mortality was accompanied by a reduction in advanced stage disease [4–7].

The English Bowel Cancer Screening Programme (NHS BCSP) began in July 2006 and rolled out incrementally across the country, achieving national coverage in 2010. It initially offered screening to all men and women between the ages of 60 and 69 years, resident in England and registered with a general practitioner. In 2010, it was extended to include everyone up to the age of 74 years inclusive. Individuals aged 75 and over may also self-refer into the programme [8, 9].

A major issue to be addressed by the UK Policy Research Unit in Cancer Awareness, Screening and Early Diagnosis (PRU), is the evaluation of the effects of the policy of CRC screening as delivered by the current national programme in terms of anticipated benefits. This issue is particularly relevant as the uptake of population-based gFOBt screening in the UK is low compared with, for example, that of mammographic screening [10], and also varies by age, sex, ethnicity and deprivation status [11–13].

In the post-RCT epoch, assessing the impact of the NHS BCSP requires the use of observational studies. Recently, Libby and collaborators [14] reported a significant 10% reduction in CRC mortality among invited individuals invited for screening as part of the UK CRC screening pilot studies in Scotland (2000–2007, three biennial rounds of invitation) when compared to a cohort of uninvited controls matched for age, gender and deprivation, and followed up to 31 December 2009.

In an ecological study, the same group found trends towards earlier stage and less advanced disease at diagnosis as well as decreasing mortality rates among individuals invited for screening as part of the pilot compared to general population individuals not yet invited for screening [15]. However, results from trends studies have limited validity [16].

We chose to address the policy questions using a retrospective matched case–control design because it is a powerful tool which has previously been used to great effect in the assessment of the NHS Cervical Screening Programme (NHS CSP), informing policy on screening intervals and age ranges [17], and recently, in the assessment of the NHS BSP [18].

Because the NHS BCSP is relatively recent (2006 onwards), long-term goals on mortality reduction may currently be difficult to assess using a retrospective design; however, this type of design will be helpful in investigating changes in incidence of advanced stage CRC, which in turn will indicate the likely future effect on mortality from the disease.

In the UK, CRC mortality has been declining in the population since the 1970s: over the last decade death rates have dropped by around 14%; in contrast, incidence rates, in particular in men, have been increasing over that same period [19, 20], making the question of the impact of the NHS BCSP on incidence of advanced stage primary CRC a very important one.

In addition, the male-to-female ratio for CRC incidence rates varies for different parts of the large bowel [21]: the majority of rectal cancer cases occur in men (63%), while colon cancer cases are approximately evenly divided between men (53%) and women (47%), suggesting the sensitivity of a particular screening strategy may differ between sexes [2].

To our knowledge, no case–control studies have been published which looked at the effect of gFOBt on CRC incidence. Two studies have been published which assessed the impact of immunochemical faecal blood test (FIT) screening on CRC incidence in Japan, in separate settings [22, 23] but only one of them investigated the effect of FIT on incidence of advanced stage disease [22]. In this study, cases (N = 349) diagnosed with advanced stage CRC (T2-T4 in TNM classification) aged 40 or over were compared to general population controls (3 per case) matched for sex, age and area of residence, with respect to screening history prior to diagnosis. The authors found a significant reduction in the incidence of advanced stage CRC in those who attended screening within 3 years prior to the date of diagnosis (OR = 0.54, 95% CI 0.30 – 0.99). No adjustments were made.

In view of the above, there is a need for a large case–control evaluation of the effect of the NHS BCSP on incidence of advanced stage CRC with appropriate methodology for coping with bias, notably self-selection bias. Meeting the above aims will entail retrieving information on tumour pathology variables, and on screening participation at other national screening programmes. This will be an ongoing biennial evaluation to ensure that the programme continues to deliver the anticipated health benefits, and to potentially improve the programme by identifying good and bad practices.

The case–control design is potentially prone to a number of biases, in particular some that could confer a bias *in favour* of screening; those will be addressed either at the design, or at the analysis stage of the study.

## Methods/Design

### Study design & objectives

The study will be a matched comparison of recently diagnosed/incident advanced stage primary CRC (colon, rectosigmoid junction and rectum) cases with general population controls free of advanced stage disease, with respect to screening exposure strictly prior to the case's date of *index/first diagnosis* (set as pseudo-diagnosis date in controls). There will be two controls per case.

The primary objective will be to determine whether the event of having been screened prior to diagnosis is superior to not having been screened in terms of incidence of advanced stage primary CRC. In addition, we plan to assess the benefit by time since last negative screen and number of screens among other measures of exposure. The secondary objective will be to consider the effect of screening on overall CRC incidence, regardless of stage.

A methodological objective of this protocol is to apply a procedure using data from RCTs and from other cancer screening programmes, in this case, from the cervical (NHS CSP) and the breast (NHS BSP) screening programmes, to adjust the analysis of the case–control studies for self-selection bias.

### Setting & source population

The background, implementation and organisation of the NHS BCSP are described in detail elsewhere [12]. For this study, all individuals who were invited to participate in the NHS BCSP in England (2006 onwards), and did not express dissent to their records being used for research, will be targeted.

The evaluation will begin with a pilot phase in one region in England using cases that were diagnosed with CRC between the 1st January 2012 and the 31st December 2013. The initial main phase of the study will then be undertaken, which will cover the whole of England or, those regions (i.e. previous cancer registries) for which tumour pathology variables will be available from 1st of January 2014. In achieving this, we shall put mechanisms in place so that the exercise can be carried out on a biennial basis.

### Participants: selection of cases & controls

#### Population of incident cases

All individuals who have had primary CRC diagnosed aged 60–89 within the specified 2-year study period will be selected. The *index diagnosis* will be either a first or a subsequent primary CRC and, therefore, individuals may have had a previous history of primary CRA or CRC (Duke A only) prior to the date of their *index diagnosis*. Cases may have died from primary CRC (as stated in part 1 of the death certificate) during the specified 2-year study period, or afterwards. DCO cases will be excluded. For subsequent phases of this evaluation (main phase onwards), individuals will not have been included as cases in previous evaluation periods, although they may have been included as controls.

#### Population of case-matched general population controls

For each case, two individuals of the same sex as the case will be selected from the general population who were registered in the same National Health Applications and Infrastructure Services (NHAIS) system as the case at the case's date of *index diagnosis*, were alive at the case’s date of *index diagnosis*, were born within 1 month either side of the case’s date of birth, and had had their first invitation to bowel screening in the same year as the case. If no matched control is found for a particular case with a date of birth within 1 month either side of the case's date of birth, the range will be expanded to 3 months either side (or 6 months either side if the case’s age at *index diagnosis* of primary CRC is over 75). For subsequent phases of this evaluation (main phase onwards), they will not have been included as population controls in previous evaluation periods.

Incident advanced stage cases and matched general population controls will be selected a posteriori by the PRU according to various designs as described in Table 1. In the initial stages of the evaluation, incident cases will be restricted to those individuals with Duke’s stage B or worse primary CRC at *index diagnosis* (Designs 1–3). Data permitting, we will also include individuals diagnosed with a Duke's stage A primary CRC during the study window but who were subsequently found to develop metastases (i.e. the cancer becomes stage B or worse) in order to avoid introducing a bias *in favour* of screening by excluding them from the population of cases and underestimating the proportion of Duke B+ tumours among screen-detected. Indeed, metastases are more likely to be early and therefore minimal and so missed in screen-detected compared to symptomatic cases; as a consequence, a minority of screen-detected tumours may be classified as having a less advanced stage leading to the underestimation of screening exposure in cases, and creating a bias *in favour* of screening.

**Table 1 Tab1:** **Proposed case–control designs and analyses**

Study	Criterion	Cases	Controls
**Design 1**			
	Previous diagnosis	None	None
		CRA	CRA
		Duke A CRC	Duke A CRC
	Index diagnosis	Duke B+ CRC	_
	Analysis	Exposure to screening prior to *first diagnosis* of case	
		Controlling for previous history of CRA & CRC	
		Adjusting for screen-detection of CRC	
**Design 2**			
	Previous diagnosis	None	None
		CRA	CRA
		Duke A CRC	Duke A CRC
	Index diagnosis	Duke B+ CRC	_
	Analysis	Exposure to screening prior to *index diagnosis* of case	
		Controlling for previous history of CRA & CRC	
		Adjusting for screen-detection of CRC	
**Design 3**			
	Previous diagnosis	None	None
		CRA	CRA
	Index diagnosis	Duke B+ CRC	_
	Analysis	Exposure to screening prior to *index diagnosis* of case	
		Controlling for previous history of CRA	
**Design 4**			
	Previous diagnosis	None	None
		CRA	CRA
	Index diagnosis	Any CRC (Duke A-D)	_
	Analysis	Exposure to screening prior to *index diagnosis* of case	
		Controlling for previous history of CRA	
**Design 5**			
	Previous diagnosis	None	None
		CRA	CRA
	Index diagnosis	Any CRC (Duke A-D)	_
		Screen-detected	Last screened in same year as case index screen
	Analysis	Exposure to screening prior to *index diagnosis* of case	
		Controlling for previous history of CRA	

CRA: Colorectal Adenoma; CRC: Colorectal Cancer.

Duke A CRC: CRC diagnosed at stage Duke A; Duke B+ CRC: CRC diagnosed at stage Duke B, C or D.

Matched general population controls will be restricted to those individuals who have never had stage B or worse primary CRC, but may have had early stage primary CRC (Duke’s stage A) or CRA prior to and including the case's date of *index diagnosis*. The majority of controls, will, however, never have had CRC (or CRA). In later stages of the evaluation, all incident cases will be considered (Design 4).

All cases and controls will appear on the HSCIC database at Exeter and will have available data on bowel, cervical (for women aged 60–64) and breast (for women aged 60–74) screening strictly prior to the date of *index/first diagnosis* of the case, depending on the analysis (that is, they have been invited to screening at least once prior, see Table 1 for details). Bowel, cervical and breast screening history as well as primary CRC pathology variables will be retrieved for all cases and controls. In addition, history of previous CRA and corresponding tumour pathology variables will be obtained.

A detailed description of the subject selection criteria and matching algorithm will be created in collaboration with our NHS partners.

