#### Exposure opportunity (frequency) bias

Once diagnosed with cancer, the cases come under clinical management and do not continue with routine screening as before. The controls, however, will continue to attend screening. To avoid a potential bias *in favour* of screening, controls are given a pseudo-diagnosis date that is the same as that of their matched case and screening history is only considered up to that date [29].

In contrast, the fact of the case having necessarily a diagnosis of cancer and a control usually not having such a diagnosis, induces an artificially higher retrospective probability of screening exposure in the cases, a bias *against screening* (i.e. the screen-detected cases will always have this screen recorded at diagnosis, whereas the large majority of controls will not at pseudo-diagnosis date). Simply excluding the detection screens of the cases from the histories would bias the results *in favour* of screening. A driver of this bias is prevalence screening and, as the NHS BCSP is a relatively young programme with at most 3 rounds at the planned start of the pilot phase (January 2012), this bias may initially be present although it is likely to decrease for subsequent evaluations.

The extent of screening opportunity bias will be investigated first, by applying an analytical correction to the odds ratio using the method developed by Duffy and collaborators [30], and second, by performing sensitivity analyses in which the date of pseudo-diagnosis for controls whose matched cases have had a screen-detected *index diagnosis* will be extended by up to 3 years, the estimated average sojourn time for each screen-detected case, to counteract the artificially higher retrospective probability of screening exposure in cases [29]. A shorter sojourn time may however be more appropriate for screen-detected tumours of stage Duke B or worse [31].

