In addition, we will perform a sensitivity analysis using screen-detected cases only. We will aim to establish whether such cases were screened less often in the past than matched controls who were screened at the time of detection screen of the case [32, 33]. In this analysis, controls that have had a screen in the same year as the *index screen* (detection screen) of their matched case will be included. The *index screen* will be excluded and the effect of prior attendance at screening on incidence of advanced stage primary CRC will be investigated. The impact of being invited to bowel cancer screening prior to *index screen* on CRC incidence may also be investigated.

But the major source of bias in case–control studies where controls are selected from the general population is potential self-selection bias [34].

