### Statistical methods

Case–control study analyses will be conducted using conditional logistic regression. Matching factors (i.e. age, area and year of first invitation to bowel cancer screening) are controlled for in design, and additional analyses will be stratified by sex and anatomical subsite. All statistical analyses will be performed using the statistical software STATA version 12 and/or R version 2.13.0.

The ***primary objective*** of this case–control will be to assess the effect of various measures of participation in bowel cancer screening *strictly prior to* the case’s date of *index/first diagnosis* on incidence from advanced stage primary CRC (see details in Table 1). The primary measure of participation to screening will be whether an individual ever attended at least one screen episode prior to diagnosis. Secondary measures will be the total number of screens, the time since last screen, the time since penultimate screen, the interval between last screen and penultimate screen, the maximum interval between 2 screens, the average interval between 2 screens, the total number of invitations, the patient's age at first screen, and the patient’s age at last screen.

‘Time since last screen’ will give estimates of the likely benefit of screening at different intervals. It will include whether that time span fell within the past two years, as this corresponds to the NHS BCSP interval and approximates the estimated preclinical screen-detectable period (PCDP).

***The secondary objective*** will be to consider the effect of screening on overall CRC incidence, regardless of stage. Similar measures of participation will be used.

*Self-selection* and *exposure opportunity* biases will be addressed using the methods described in the *Bias & Effect modification* section.

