Secondary analyses will consider time since last screen stratified by age at diagnosis/pseudo-diagnosis, by *index/first tumour* detection mode, and by region (Main phase only). Analysis may be adjusted for stage at diagnosis. The effect of attending a screen in a particular 5-year age band (e.g. 60–64), in the pilot phase, or 2-year age band (e.g. 60–61), in the main phase, on incidence from advanced stage primary CRC in the subsequent 5-year age band (i.e. 62–66 or 65–69, respectively) will also be investigated, as performed for the cervical screening audit [17]. The results of this analysis should be very similar to those obtained from the analysis of ‘time since last screen’ after stratifying the analysis by age at diagnosis/pseudo-diagnosis.

In the main phase of the study, the effect of invitation to bowel screening and attendance at screening prior to the *index screen* of the case will also be assessed among screen-detected cases matched to controls screened within the same screening interval (Table 1 Design 5).

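### Table 1 defines Design 5 exposure up to the index diagnosis, which counts the detection screen and makes the ever/never odds ratio inestimable; the text uses the index screen, and the control window also differs

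*Protocol article*

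**What the plan says.** **Table 1, Design 5.** Cases are screen-detected, with index diagnosis "Any CRC (Duke A-D". Controls are "Last screened in same year as case index screen". The analysis row reads "Exposure to screening prior to *index diagnosis* of case", the same wording as in Designs 2 to 4, and does not exclude the index screen.

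**Exposure opportunity (frequency) bias.** Controls receive the case's diagnosis date as a pseudo-diagnosis date, and "screening history is only considered up to that date". The section notes that "the screen-detected cases will always have this screen recorded at diagnosis". It then adds a sensitivity analysis in screen-detected cases only, with controls who had a screen in the same year as the case's index (detection) screen. There the index screen is excluded and "the effect of prior attendance at screening on incidence of advanced stage primary CRC will be investigated". Design 5 is not named.

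**Statistical methods.** The model is conditional logistic regression. The primary exposure is "whether an individual ever attended at least one screen episode prior to diagnosis". The last paragraph plans, for the main phase, to assess invitation and attendance before the index screen among screen-detected cases "matched to controls screened within the same screening interval (Table 1 Design 5". It states no stage.

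**The concern.** A screen-detected case has, by definition, attended a screen before diagnosis. If exposure is any attendance before diagnosis, the rule that selects the cases also fixes their exposure, and nothing is left to compare on the primary measure. Statistical methods refers the reader to Table 1 for details of the exposure windows, so an analyst who follows the Design 5 row would build the wrong variable.

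Two further differences affect the same analysis. The controls are chosen by three different rules in three places. The only screen-detected design in the table takes any stage, while the sensitivity analysis in the bias section names advanced-stage cancer as its outcome. At stake is one of the planned checks on exposure opportunity bias and the main-phase Design 5 result. The primary estimate itself is not affected.

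**Working it through.** The article gives no sample size or exposure figure for Design 5, so there is no stated number to reproduce. The check sets the rules side by side, followed by a small calculation.

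**1. The rules compared**

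| Item | Table 1, Design 5 | Exposure opportunity bias section | Statistical methods, last paragraph |
|---|---|---|---|
| Exposure counted | before index diagnosis | index screen excluded | before index screen |
| Controls | last screened in the same year | had a screen in the same year | screened within the same interval |
| Stage | any (A to D) | advanced | not stated |
| Names Design 5 | yes | no | yes |

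Statistical methods gives the programme interval as two years, so the interval window is wider than the one-year window. Last screened and had a screen also differ: a control with a later screen can qualify under the second and not the first.

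**2. Likelihood under the tabulated rule.** Take a set with one case and two controls. The case is always exposed; let k of the two controls be exposed (k = 0, 1, 2). With odds ratio θ, the conditional likelihood contribution is

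θ / [(1 + k)θ + (2 − k)].

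- k = 2: the contribution is 1/3 for every θ, so the set carries no information.
- k = 0 or 1: the contribution rises with θ towards 1/(1 + k), so it is largest as θ goes to infinity.

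No set can have an unexposed case, so nothing pulls the estimate back. If all sets have k = 2, θ is undefined; if any has k < 2, the estimate is infinite.

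**3. Which of the two occurs.** This depends on whether a control's same-year screen can fall after the pseudo-diagnosis date. Assume screen dates uniform within the year and a lag of L years from index screen to diagnosis. Then

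P(control's screen precedes the case's diagnosis) = 1 − (1 − L)²/2.

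- L = 0: 1 − 1/2 = 50%
- L = 2/12: 1 − 0.694/2 = 65%
- L = 6/12: 1 − 0.25/2 = 87.5%

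For illustration, borrow the pilot's anticipated exposure (55% cases, 59% controls, from the Power calculation section) as prior attendance, independent within pairs, with a 2-month lag and 20,000 simulated 1:1 pairs:

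| Rule | Cases exposed | Controls exposed | Case-only pairs | Control-only pairs | Matched OR |
|---|---|---|---|---|---|
| Table, all controls qualify within the truncated history | 100% | 100% | 0 | 0 | undefined |
| Table, calendar-year selection | 100% | 86% | 2,864 | 0 | infinite |
| Text, concurrent screen not counted in either group | 55% | 58% | 4,598 | 5,198 | 0.88 |

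The 86% agrees with direct arithmetic: 0.653 + 0.347 × 0.59 = 0.858. For the last row, direct arithmetic gives (0.55 × 0.41)/(0.45 × 0.59) = 0.2255/0.2655 = 0.85; the 0.88 is one simulation run. Neither value predicts the study result. They show only that the ratio is estimable under the text's rule.

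**4. Other exposure measures.** Number of screens would still vary under the tabulated rule, with a minimum of 1 in cases. Time since last screen would largely reflect the screen used for selection.

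**The case against.** The strongest reply is that the text already answers the point. Statistical methods cites Design 5 by name and counts attendance before the index screen, and the bias section excludes that screen. The Design 5 row repeats the wording of Designs 2 to 4 and may be a carry-over. This stands as evidence of intent: the planned analysis is sound and the defect is in its tabulated specification. It does not remove the contradiction, because the table is where the reader is sent for details.

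It can also be said that detailed selection criteria and the matching algorithm are deferred to a later document. That covers detail still to be added. It does not cover three stated rules that differ.

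Several stronger readings are tempting and are not supported:

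- *That this is the only safeguard against exposure opportunity bias.* The same section first plans an analytical correction to the odds ratio, then an extension of the controls' pseudo-diagnosis date by up to 3 years. The screen-detected analysis is the third check.
- *That the index screen would be dropped for cases only, driving the odds ratio towards 0.* No sentence says that a control's concurrent screen counts as prior exposure. The bias section contrasts past screening with screening at the time of detection, which suggests the same treatment in both groups. It could be more explicit, but no bias follows from the text.
- *That sets whose index screen belongs to the first invitation must be removed.* Controls are matched on year of first invitation. Sets with no earlier opportunity in either group are concordant and carry no weight in the conditional model. Removing them would also take away the invitation contrast that Statistical methods plans.
- *That the stage conflict is proven.* It assumes that the bias section describes Design 5, which it does not name. These may be two related analyses.

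**Conclusion.** The Design 5 exposure row is wrong as written. Every case is exposed by selection, and the ever/never odds ratio is undefined or infinite, depending on whether control histories are truncated before or after the qualifying screen. Full exposure is certain for cases. For controls it holds only if the qualifying screen must fall before the pseudo-diagnosis date. The conclusion for cases rests on no numerical assumption; the 12.5% to 50% share of controls whose screen falls too late rests on uniform dates and a lag of 6 to 0 months.

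The row contradicts both places in the text that describe a screen-detected analysis. The control window conflict is also real: same year against a two-year interval, and last screened against had a screen. The stage difference needs a clarifying statement and is not an established contradiction.

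A reader might infer that Design 5 is void or that the primary result is left unprotected. Neither follows, since the text gives an estimable analysis and two other checks are planned. This should be corrected before the analysis is run.

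**What to change.** - In Table 1, Design 5, change the exposure row to screening prior to the index screen of the case.
- State, in the table or in the bias section, that the control's qualifying concurrent screen is likewise not counted. A date cut-off alone would not ensure this: with uniform dates, about half of the same-year control screens precede the case's index screen (the L = 0 result above).
- Use one control window in Table 1, the bias section and Statistical methods, and say whether a control may have a later screen. Same year already appears in two of the three places, so it is the smaller edit.
- Name the stage for each screen-detected analysis: Duke B+ for the bias section's check of the primary analysis, and any CRC as the companion to Design 4.

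The cost is one table row and a few sentences. Restricting the check to Duke B+ screen-detected cases leaves fewer sets and a wider confidence interval; the article gives no count from which to size this. No change to data collection is needed, since full screening histories and detection mode are already on the variable list.
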